# STUDY OUTLINE

## Type of experiment

This study falls within the scope of interventional research that studies the human body, with minimal risks and constraints. This is due to the fact that, on the one hand it evaluates a POTs intervention, which is already being used by the French Ministry of the Armed Forces, and, on the other hand, it requires the collection of non-invasive biomedical (physiological and psychological) data, which provide no information regarding the individual’s health.

The project’s objectives will be met using a prospective, controlled cohort study. This open study will be conducted in a sample of healthy volunteers, with direct benefits. It is one of various activities typically implemented during physical activities in the military context to ensure that personnel remain in good health.

## Study outline

In order to guarantee compliance with the experimental protocol over the two years of the study (see paragraph 3.3 for a detailed explanation), the active control intervention will be carried out in the first year (year Y), while the POTs intervention will be carried out in the second year (year Y+1).

The study will be carried out in the following six units the in the French armed forces :

1. the National Gendarmerie (Versailles-Satory, 78)
2. the 10th Air Parachute Commando (Orléans, 45)
3. the 1st Marine Infantry Parachute Regiment (Bayonne, 64)
4. the 13th Parachute Dragoon Regiment (Souge, 33)
5. the Paris Fire Brigade (Villeneuve-Saint-Georges, 94)
6. the Fusiliers Marins [Navy Riflemen] School (Lorient, 56)

The study will take place during the selection courses organized by each unit, and will last three weeks.

### The intervention

The POTs intervention will consist of practical courses run by the designated POTs instructor in each military unit. This person is a member of the military who has completed the POT trainer course delivered by the French Centre National des Sports de Défense. The intervention is divided into six, one-hour sessions, spread over three weeks, with two sessions per week. The first two sessions will be scheduled at the start of the selection course (ideally the day before it begins).

The intervention will include theoretical instruction and practical exercises in POTs that have been identified as useful in increasing body awareness (paying attention to breathing, muscle relaxation, mental imagery). The contents of the six sessions will be established and validated beforehand by POTs instructors from the six military units, under the supervision of the POTs instructor who coordinates the intervention.

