## Secondary objectives

The study has 4 secondary objectives:

1. The first is to test the mechanistic hypothesis that POTs reduce the risk of fall-related injury by improving postural awareness.
2. The second is to test the mechanistic hypothesis that POTs reduce the risk of fall injury by decreasing the intensity of the psychobiological stress response during physical activities in the military context.
3. The third is to use machine learning techniques to develop a predictive model of the risk of fall injury, based on a clinical test (BESS) and paraclinical (posturography) measurements taken before physical activities begin.
4. The fourth is to evaluate the persistence over time of the effectiveness of a POT intervention in reducing the risk of fall injury. The assessment will be based on participants who continue to engage in physical activities after the end-of-study visit (and who complete the selection course); the analysis will compare the rate of fall injuries for POTs and active control groups.

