### The active control

The active control will unfold in the same way as the POTs intervention: there will be six one-hour sessions, spread over the three weeks of the study, with two sessions per week. These sessions will consist of exercises (details of the sessions are available in APPENDIX 2 ) that focus on high-level cognitive processes such as reasoning, information processing and creativity. They will be divided into two p3arts: the first, theoretical component will describe the processes that will be the focus of the session, and the second, practical component will focus on exercises.

These sessions will be carried out under the supervision of the person responsible for the POTs intervention that will take place the following year (the POTs instructor).

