## Secondary endpoints

Criteria for meeting the study’s four secondary objectives are as follows:

- - 1. The first secondary objective comprises two evaluation criteria: 1) self-reported scores on the Postural Awareness Scale (APPENDIX 3) pre- and post-intervention, and at the start of each session; 2) variation in measures of postural balance pre- and post-intervention.
    2. The second objective also comprises two criteria: 1) self-reported scores on Cohen’s Perceived Stress questionnaire (APPENDIX 3) pre- and post-intervention, and at the start of each session; 2) variation in measures of allostatic load in saliva pre- and post-intervention (the corticotropic axis: cortisol, DHEA, oxidative stress; the autonomic nervous system: alpha amylase and chromogranin A).
    3. The evaluation criterion for the third secondary objective will be the correct prediction of the risk of fall injury by the machine learning model.
    4. The evaluation criterion for the fourth secondary objective will be the rate of fall injuries in each of the two groups (POTs *vs.* active control), in the period between the end of the study and the end of the selection course. Information about when each participant left the course will be collected from the physician responsible.

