## Study visit schedule

The day before the start of the selection course, candidates will receive a group briefing from the investigator or one of his or her collaborators, together with a letter informing them about the study. Candidates will be given several hours to reflect on whether they would like to participate before the inclusion visit.

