### Inclusion visit

The inclusion visit will take place the day after the group information session, and before any examinations related to the study. During the visit, the investigator or one of his or her collaborators will ask the participant if they want to take part in the study, and will inform him or her:

- of the objective of the study, and any constraints,
- foreseeable risks and expected benefits,
- that personal data collected during the study will be held and processed digitally, and state his/her rights regarding access, opposition and rectification,
- that samples will be conserved for scientific purposes after the study has ended, and obtain consent.

The investigator, or a colleague will answer any questions the participant may have. The latter will then have 15 minutes to reflect on his or her decision to take part in the study. Formal agreement will be obtained by signing the consent document (three copies).

Any changes to the study that impact either patient care, or benefits, risks and constraints will be presented in a new information document. The same procedure will be used to inform those concerned.

The various copies of the information document and the consent form will then be distributed as follows:

- A copy of the information document and the signed consent form will be given to the participant.
- The original will be held by the investigating medic in a safe place that cannot be accessed by third parties.

A copy of each consent form will be sent to the sponsor or its representative after inclusion or, at the latest, at the end of the study, in accordance with the procedures communicated.

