### Initial evaluation visit

The initial evaluation visit will take place immediately after the inclusion visit for subjects who have given consent to participate. During this visit, the investigator, or one of his or her collaborators, will collect clinical data (age, height, weight and gender), run the BESS, and collect posturography measurements. The participant will then complete a medico-demographic questionnaire, together with questionnaires to measure postural awareness (the Postural Awareness Scale) and perceived stress (Cohen’s Perceived Stress questionnaire). Finally, a 4 ml saliva sample will be collected.

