### Follow-up visits

A follow-up visit will be carried out just before each session of the POTs and active control interventions (the schedule for which is shown in Figure 4). During the follow-up visit, the participant will complete self-report questionnaires measuring postural awareness (the Postural Awareness Scale) and perceived stress (Cohen’s Perceived Stress).

Participants who suffer a fall trauma during the course will attend an additional follow-up visit, which will take place on the day of the injury. The military medic, or one of his or her assistants, will collect medical information relating to the trauma, and carry out a posturography measurement. The participant will then complete questionnaires measuring postural awareness (the Postural Awareness Scale) and perceived stress (Cohen’s Perceived Stress).

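### The preferred day for the first two sessions falls one day before the dated consent and initial evaluation visits (minor)

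*Protocol*

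**What the plan says.** All references are to the Protocol.

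- **The intervention** plans six one-hour sessions over three weeks, two per week. On the first two it says: "The first two sessions will be scheduled at the start of the selection course (ideally the day before it begins").
- **The active control** extends this to the comparison group: "The active control will unfold in the same way as the POTs intervention".
- **Study visit schedule**: "The day before the start of the selection course, candidates will receive a group briefing".
- **Inclusion visit**, where consent is signed: "The inclusion visit will take place the day after the group information session, and before any examinations related to the study".
- **Initial evaluation visit** (BESS, posturography, questionnaires, saliva): "The initial evaluation visit will take place immediately after the inclusion visit".
- **Follow-up visits**: "A follow-up visit will be carried out just before each session of the POTs and active control interventions".
- **Secondary objectives** bases the objective 3 prediction model on measures "based on a clinical test (BESS) and paraclinical (posturography) measurements taken before physical activities begin".
- **Secondary endpoints** defines one objective 1 criterion as "variation in measures of postural balance pre- and post-intervention". The salivary markers of objective 2 are defined in the same pre-to-post way.

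**The concern.** The protocol recommends a day for sessions 1 and 2 that its own visit calendar cannot accommodate in the right order. On the recommended day candidates are only being briefed; they sign consent and are measured the next day.

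Two things would be at stake if a unit acted on the recommendation.

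- **Consent.** The distinction between care and research classes both programs and all measurements as research activities. Two sessions, and the questionnaire visits attached to them, would take place before written consent.
- **Baseline.** Posturography and saliva have one planned value before the intervention, at the initial evaluation. The analysis of secondary objectives 1 and 2 compares these before and after within the POTs group by paired means. No control contrast would offset a baseline taken after a third of the program.

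The slip is plausible because different people act on different sections. Under General logistics, the coordinating team and unit medical staff run inclusion and evaluation, while the POTs instructor runs the visits before each session. The instructor also leads the POTs sessions and supervises the control sessions, and this happens in six units.

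**Working it through.** The protocol gives no figure to reproduce here; the check is calendar arithmetic.

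**Notation.** Day 0 is the first day of the selection course, b the briefing day, s the day of sessions 1 and 2.

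**Inputs**
- b = -1 (Study visit schedule)
- inclusion and consent = b + 1 (Inclusion visit)
- initial evaluation = same day as inclusion (Initial evaluation visit)
- preferred s = -1 (The intervention; same for The active control)

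**Step 1: dates as written.** Inclusion = -1 + 1 = 0, and evaluation = 0. Gap between the preferred sessions and consent: 0 - (-1) = 1 day, with the sessions first.

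**Step 2: is any schedule consistent with the binding text?** Yes. The main clause asks only for the start of the course. With s = 0, held after the evaluation, the main clause and all the visit sections are met.

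**Step 3: when could the preferred day be used?** The evaluation must come no later than day -1, so b + 1 ≤ -1, which gives b ≤ -2. With b = -2, consent and evaluation fall on day -1 and can precede the sessions that day. With b = -3, they fall on day -2. The smallest shift of the briefing is one day.

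**Step 4: sessions before consent and evaluation**

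| Schedule | Sessions first |
| --- | --- |
| Preferred day, visit dates as written | 2/6 = 33% |
| Sessions on day 0 after evaluation | 0/6 |
| Briefing on day -2 or earlier, evaluation before the sessions | 0/6 |

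**Step 5: what is lost in the first row**

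| Measure | Consequence |
| --- | --- |
| Posturography, saliva | No value before session 1; the paired comparison starts after session 2 |
| Postural Awareness Scale, perceived stress | Also collected just before each session, so a value before session 1 exists (though obtained before consent) |
| BESS | Not repeated at the End-of-study visit, so no pre/post comparison to distort |
| Objective 3 predictors | Required before physical activities, not before sessions; met if taken ahead of the first activity on day 0 |
| Primary endpoint | Injuries recorded during the course and compared between groups on the same timetable; largely unaffected |

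The size of any bias in the posturography and saliva comparisons cannot be derived from the document. If the first two sessions have an effect, a late baseline would most plausibly shrink the measured change.

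**The case against.** The strongest reply is that nothing binding conflicts. The word *ideally* marks a preference, and a preference that cannot be met gives way. The intended order is also recoverable. Randomization assigns the programs to included participants, the initial evaluation is for those who have consented and follows inclusion at once, each session has a study questionnaire visit attached, and the endpoints call for pre-intervention values. A unit would have to overlook all of this to go wrong. Figure 4, which Follow-up visits names as the session schedule, and Table 1 are not shown and may draw the evaluation ahead of session 1.

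Most of this stands and sets the severity. A reader might infer that the protocol schedules sessions before consent, or that it never orders the two. Neither is supported: the main clause can be met on day 0 and the order is implied in several places. A reader might also infer that every baseline for objectives 1 and 2, and the objective 3 predictors, would be spoiled. The second table under the check shows that the exposure is limited to posturography and saliva.

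What does not stand is that there is nothing to correct. The figures might lower the practical risk, but they cannot reconcile dates given in the text. The several hours of reflection in Study visit schedule could suggest inclusion on the briefing day, but Inclusion visit says the following day outright. The section an instructor would consult on session timing also contains no rule that session 1 waits for consent and evaluation.

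**Conclusion.** The point holds as a minor inconsistency of dates. The stated ideal day for sessions 1 and 2 is one day earlier than consent and the initial evaluation. Followed literally with the visit dates unchanged, it puts 2 of 6 sessions before written consent and leaves posturography and saliva without a true pre-intervention value. Under any other reading the figure is 0 of 6.

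This rests on three assumptions: day 0 is the first day of the course; the visit dates in the text govern; and questionnaires are collected before every session, as Follow-up visits says. On the last, the Research summary counts only four follow-up visits. If sessions 1 and 2 had none of their own, their questionnaires would not precede consent, but the two scales would also lack a value before session 1 in the adverse case. The text alone cannot show whether any unit would follow the preference.

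**What to change.** **Main change, in The intervention.** Delete the parenthetical preference for the day before the course. Add one sentence: session 1 takes place only after written consent and the initial evaluation, on day 0 and before any course activity. This also secures the objective 3 requirement on timing. The active control inherits the change. The cost is one deleted phrase and one added sentence; day 0 must have room for the evaluation and two one-hour sessions before course activity starts.

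**Alternative, where a unit can make candidates available.** Move the briefing to day -2 or earlier, so that consent and evaluation precede sessions on day -1, and add the same ordering rule. The cost is an earlier briefing and, with a briefing on day -2, a heavier day -1 carrying consent, all baseline measures and two sessions. The document does not show whether the six units could manage this, which is why it is the second choice.

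Under either option, do not use a posturography or saliva measurement taken after session 1 as a pre-intervention value.

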### The active control

The active control will unfold in the same way as the POTs intervention: there will be six one-hour sessions, spread over the three weeks of the study, with two sessions per week. These sessions will consist of exercises (details of the sessions are available in APPENDIX 2 ) that focus on high-level cognitive processes such as reasoning, information processing and creativity. They will be divided into two p3arts: the first, theoretical component will describe the processes that will be the focus of the session, and the second, practical component will focus on exercises.

These sessions will be carried out under the supervision of the person responsible for the POTs intervention that will take place the following year (the POTs instructor).

### Summary

[figure not shown]

**Figure 4** – Schedule of the study for a given year. The same schedule will be followed during the two years of the study, only the content of the sessions will change: the active control in year Y, and the POTs intervention in year Y+1. Timeline for each study participant (in weeks). V1: inclusion visit (saliva sampling, posturography, and the BESS). V2: end-of-study visit (saliva sampling, and posturography). Gray triangle: a one-hour session, either during the active control program (first year), or the ORAF intervention (second year). Star: Self-administeed questionnaires (PAS, PSS, fatigue).

## Randomization

There will be no randomization (POTs versus active control) at the individual level (i.e., for each participant in each military unit). This is not possible due to the risk of participants in the POTs group influencing those in the active control group (contamination bias). The conditions under which the selection course is carried out mean that participants in both groups are in close contact with each other. Moreover, it is possible that running the two interventions at the same time may undermine the desired team cohesion. Hence, we have chosen to carry out the study over two successive years (years Y and Y+1):

1. Participants included in year Y will follow the active control program.
2. Participants included in year Y+1 will follow the POTs program.

The order of the two interventions (active control followed by POTs) is deliberately not randomized between units, to ensure that the research protocol is respected throughout the study. If the POTs intervention was run in year Y, and was found to be beneficial, it would be very difficult to expect participating units to set up an active control in year Y+1, as it is unrealistic to expect them to abandon a program with potential benefits for candidates.

# ELIGIBILITY CRITERIA

## Recruitment procedures

Participants will be volunteers recruited from among candidates for the selection course organized by the various units. They will be in good health and physical condition, as they will have been declared medically fit to enroll in the course. Participation in the study will be open to all candidates who qualify for the selection course.

## Inclusion criteria

- Informed written consent to participate in the study
- Candidate for the selection course
- Male or female, over 18 years of age
- Eligible for benefits under the French Social Security scheme

## Exclusion criteria

- Participants who have already completed an ‘advanced’ POTs training program (> 10 hours)^[[3]](#footnote-3)^
- Refusal to participate
- Person covered by articles L1121-5 to L1121-8 of the public health code, as follows:
  - A pregnant^[[4]](#footnote-4)^, parturient or nursing woman,
  - A person detained following a judicial or administrative decision,
  - Persons who are subject to psychiatric monitoring under articles L3112-1 and L3113-1, and who are not covered by the provisions of article L1121-8,
  - Adults made a ward of court, or who are unable to give their consent.

# EVALUATION CRITERIA

## Primary endpoint

The primary endpoint will be the rate of fall injuries following a loss of balance in each of the two groups (POTs *vs.* active control).

A fall injury will be recorded by the medic responsible for providing healthcare during the selection course. The injured participant will be required to attend an additional follow-up visit on the same day after the initial medical consultation.

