Against this background, the POSITION project aims to study the cognitive mechanisms involved in body awareness, both as a risk factor in fall injury, and as a target for a prevention strategy that aims to reduce the injury rate by improving postural control.

This research project was prompted by epidemiological observations carried out during the French Marine Commando Selection Course (STAC). Medical unfitness due to incapacity is the leading cause of failure (70%). Acute trauma is the principal pathology (60%), typically involving the lower limbs (Bertrand, 2016; Longin, 2015; Morinière, 2013). A review of the circumstances surrounding the trauma highlighted that a fall due to a loss of balance was the cause in 90% of cases (Bertrand, 2016). These data suggest that postural balance could play a role in the injuries encountered during the STAC. The activities that candidates must undertake require them to have extremely good postural balance: trainees carry heavy loads (a combat bag and a weapon, weighing 15 kg) for prolonged periods, and complete extreme challenges that are run at-height in all weather conditions. Epidemiological data collected during the course show that the leading activity resulting in trauma is the ‘jungle’ challenge, which involves overcoming obstacles up to 5 meters high with no safety net (Morinière, 2013). Moreover, preliminary (unpublished) epidemiological data collected from other military units (the National Gendarmerie, the 1st Marine Infantry Parachute Regiment, the 13th Parachute Dragoon Regiment, the 10th Air Parachute Commando, and the Fusiliers Marins [Navy Riflemen] School, Paris Fire Brigade) seem to confirm the high rate of trauma linked to a loss of postural balance during physical activities.

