**Questionnaire de Stress perçu de Cohen**

**
[figure not shown]
**

1. At the time the protocol was submitted, the Optimization of the Resources of the Armed Forces (ORAF) program was known as Potential Optimization Techniques (POT). [↑](#footnote-ref-1)
2. In the remainder of this document, and to improve readability, we use the term ‘fall injury’ to refer to an injury (or trauma) due to a fall resulting from a loss of balance. [↑](#footnote-ref-2)
3. ‘Advanced’ POTs training is defined as training that lasts longer than the initial training offered by the Ministry of the Armed Forces (10 hours). [↑](#footnote-ref-3)
4. All female candidates must provide evidence of a negative pregnancy test to take part in the selection course. [↑](#footnote-ref-4)

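### The primary event rests on an arm-aware medic's judgement of injury mechanism, and without an all-trauma record a change in that judgement between years could not be clearly seen

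*Protocol*

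**What the plan says.** The Primary endpoint section of the Protocol states: "The primary endpoint will be the rate of fall injuries following a loss of balance in each of the two groups". Footnote 2 says the term is used "to refer to an injury (or trauma) due to a fall resulting from a loss of balance". No working criteria separate such an injury from other trauma.

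On ascertainment, the same section says: "A fall injury will be recorded by the medic responsible for providing healthcare during the selection course". Under General logistics, the extra injury visit is run by the unit's medical officer or a collaborator. No independent or masked review of mechanism is described.

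On knowledge of the arm, Type of experiment says: "This open study will be conducted in a sample of healthy volunteers, with direct benefits". The Randomization section fixes the order for all units: "Participants included in year Y will follow the active control program" and "Participants included in year Y+1 will follow the POTs program".

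On data capture, the Schedule row of the Research summary and the Follow-up visits section tie the extra visit, where details of the trauma are collected, to fall trauma only. Clinical parameters lists injury history and demographic and body measurements, with no item for other trauma during the course. Neither the Secondary endpoints nor the Statistical methods contain an all-trauma outcome.

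**The concern.** Whether an injury becomes an event depends on a judgement of cause: did this participant fall because balance was lost? The person recording it can know the arm, since the whole unit is on control in one year and on POTs in the next. The Randomization section itself expects units to be reluctant to give up POTs once they look beneficial, so opinions about the programme among course staff are plausible.

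Suppose the threshold for calling an injury a loss-of-balance fall differs between the years. The fall-injury rates then differ even if the number of injured participants is the same. A lower share in the POTs year resembles prevention, and a higher share hides it. The simplest check is whether total trauma moved with fall trauma, and that needs data the Protocol does not plan to collect. A statistical analysis plan can add a model, but it cannot analyse injuries that were never recorded.

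**Working it through.** **Inputs.** From Calculating the number of subjects required: 50% (control) and 35% (POTs), two-sided 0.05, power 0.80, 10% drop-out, 200 per group. Evaluable per group: 200 × 0.90 = 180. From Current knowledge, on the marine commando course (STAC): "a fall due to a loss of balance was the cause in 90% of cases". The STAC is not named among the six study units, so its use here is an assumption. A two-proportion z-test stands in for the planned Cox and log-rank analysis, in line with the Protocol's own sample-size inputs.

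**1. The plan's own figure.** With mean proportion 0.425:

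n = [1.96·√(2·0.425·0.575) + 0.842·√(0.25 + 0.2275)]² / 0.15², which gives 170.

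Continuity correction gives 183. Drop-out then gives 183/0.9 = 204 or 183 × 1.1 = 202. The stated 200 is reproduced to within 3%, so the sample size is not in question.

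**2. Effect of an attribution shift when POTs does nothing.** All-trauma rate T = 0.50/0.90 = 0.556 in both years. Observed fall rate in the POTs year = T × a, where a is the share attributed to falls. P(reject) comes from z = (d − 1.96·SE₀)/SE₁, with d = 0.50 − T·a, SE₀ pooled and SE₁ unpooled, plus the opposite tail.

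| a in POTs year | Observed fall rate | P(p<0.05) | of which favours POTs |
|---|---|---|---|
| 90% | 0.500 | 5.0% | 2.5% |
| 85% | 0.472 | 8.2% | 7.6% |
| 80% | 0.444 | 18.4% | 18.3% |
| 70% | 0.389 | 56.5% | 56.4% |

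To reproduce the whole planned contrast, a must fall to 0.35/0.556 = 63%. A rise to 95% gives T·a = 0.528, so d = −0.028, the mirror image of the 85% row: about 8% again, mostly against POTs.

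**3. What an all-trauma analysis costs in power.** If non-fall trauma stays at 0.556 − 0.50 = 0.056, the all-trauma contrast is 0.556 against 0.406. At 180 per group:

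z = (0.150 − 1.96·0.0527)/0.0521 = 0.90, so power is 0.816.

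The fall-only contrast of 0.50 against 0.35 has 0.824. With a fall share of 80% or 70%, all-trauma power is 0.82 or 0.85.

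**4. Would comparing the fall share expose a shift?** Expected injured per group: 180 × 0.556 = 100. Testing 0.90 against a with 100 per group:

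- a = 85%: (0.05 − 1.96·0.0468)/0.0466 = −0.89, so about 19%
- a = 80%: (0.10 − 1.96·0.0505)/0.0500 = 0.02, so about 51%
- a = 70%: (0.20 − 1.96·0.0566)/0.0548 = 1.63, so about 95%

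**5. Would a same-direction rule protect the claim?** Simulation of the step 2 scenarios (400,000 runs) gives significant fall results favouring POTs in 7.8%, 18.4% and 56.5% of trials. Requiring all-trauma to point the same way as well leaves 7.8%, 17.9% and 41.6%. Total trauma and fall trauma are strongly correlated, so the rule removes very little.

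**The case against.** The strongest reply is that nothing here is an error. The event is defined, the assessor is named, the injury visit gathers details of the trauma, and a supportive model is ordinary analysis-plan content. That is right about the model. It does not cover data capture, which the Protocol fixes and limits to fall trauma.

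Three stronger readings are tempting, and the documents do not support them.

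- **That the endpoint is biased towards POTs.** Nothing shows that attribution will shift, or which way. A medic alerted to falls by the second year might attribute more injuries to them.
- **That a small shift would pass for prevention.** Five points move the rejection rate only from 5% to about 8%, and the planned effect needs a drop from 90% to 63%.
- **That nothing in the plan could reveal a shift.** Early leavers have an end-of-study visit whatever their reason, the time of leaving is collected, the flow chart gives reasons for exclusion from analysis, and monitors compare case report forms with medical records. These are partial traces. None is a trauma record by mechanism, and someone injured without leaving the course would be missed.

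It is also fair to say that all-trauma counts still depend on the same medic and on participants seeking care, and that arm is fully confounded with year. Both points stand. An all-trauma analysis addresses attribution only.

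**Conclusion.** The point holds as a vulnerability in endpoint ascertainment. A mechanism-dependent event, an assessor who can know the arm, and study injury data limited to falls together mean that a difference in attribution between years would bias the primary result without being clearly visible.

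Under the stated assumptions the chance of a spurious significant result is about 8%, 18% or 56% when attribution in the POTs year falls to 85%, 80% or 70%. The risk is minor for a small shift and serious for a large one. The figures depend on the borrowed 90% share, on equal true trauma in both years and on 180 evaluable per group. The size and direction of any real shift are unknown. This is a cheap improvement to make before data collection, and the sample size is unaffected.

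**What to change.** In Primary endpoint and Follow-up visits, have the course medic record every acute trauma in participants in both years, with its date and its mechanism in fixed fields.

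Pre-specify the same Cox model on all acute trauma as a supportive analysis, reported as an estimate with its confidence interval beside the primary result. Compare the share of trauma attributed to falls between groups. If the all-trauma effect is clearly smaller than the fall effect, or the fall share differs, state that the primary result may reflect attribution.

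Allow for what real prevention would do. With non-fall trauma unchanged, the risk ratio is 0.406/0.556 = 0.73 for all trauma against 0.35/0.50 = 0.70 for falls, and the fall share drops from 90% to 0.35/0.406 = 86%. So show the non-fall rate too. Prevention leaves it at 5.6%, whereas attribution of 80% in step 2 would raise it to 0.556 × 0.20 = 11.1%.

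Do not make the claim conditional on both results merely pointing the same way, since that gives almost no protection at small shifts.

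Cost: one form entry per non-fall trauma, one further model, and slight dilution (all-trauma power about 0.82 if non-fall trauma is unaffected). No extra staff are needed. Other differences between the years, and under-recording of injuries of every kind, remain.
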